### Data analysis

The main outcome of recruitment feasibility will be reported, as frequency of patients recruited during the study period. Reasons for screening or randomisation failure will be collated and presented as frequencies. Descriptive data will include an evaluation of eligibility, recruitment, acceptability of and adherence to the intervention, with 95% CIs. Secondary outcome measures, including PROMs, will be assessed before and after the intervention to establish any possible trend in the intervention effects over time and understand the variability in data. The completion of outcome measures will be reported and changes in outcome assessments relative to baseline assessments will be analysed using appropriate parametric or non-parametric statistics based on the characteristics of the data. All tests will be two-sided with an alpha level of 0.05. Estimates of population variances of outcomes for future power calculations will use the upper 80th percentile of confidence intervals around the estimates will be carried out. In addition, individual performance and movement quality in the VR intervention will be monitored and measured during the 12-week programme, every time the patient completes a training session, to determine any improvement in comparison to baseline measurements.

The qualitative interviews will be used to obtain views on participants’ acceptance of the technology, factors influencing their participation in the trial, any unexpected benefits or adverse effects experienced, as well as their experiences with pain and any impact on their overall function and exercise. Data will be managed using NVivo software. Data will be analysed using Braun and Clarke’s thematic analysis.

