## Introduction

 Osteoarthritis (OA) is a costly major worldwide challenge, impairing function and quality of life. It is one of the leading causes of musculoskeletal pain and disability worldwide,^1^ mainly affecting the knees and hips. The global prevalence of knee OA in 2020 was approximately 7.6% of the global population^2^ and, with an ageing population, the projected rate of years lived with disability is estimated to be 118.5 per 100 000.^3^ Persistent pain is the dominant symptom and can be associated with widespread sensitisation, which may impair neuromuscular control.^4^ OA pain fluctuates, often with intermittent and severe flares from which both symptomatic and functional recovery might be incomplete. Ultimately, pain impairs the differential control of muscles around the painful area, leading to a loss of functional independence and a profound reduction in physical activity, quality of life and mental well-being.^5 6^

Physiotherapy-based exercise is a key non-pharmacological intervention for OA pain management.^7 8^ It offers a safer, low-cost alternative to surgery and long-term medication.^9^,^11^ Exercise reduces pain through multiple mechanisms, including activating endogenous pain inhibition (exercise-induced hypoalgesia),^12^,^14^ improving muscle perfusion^15 16^ and enhancing joint stability during daily activities.^17 18^ However, exercise benefits diminish without continued adherence. A major challenge in translating clinical trial efficacy into real-world outcomes is poor long-term compliance. Prolonged treatment is essential for sustained pain relief and functional improvements.^19^ Patients need skills and motivation to maintain exercises after clinical support ends, as delayed intervention can compromise future treatments like arthroplasty.^20^

Home-based physiotherapy is a promising solution, accommodating individual needs, time constraints and preferences. Studies suggest it can be as effective as clinic-based therapy,^21^,^24^ but adherence remains a concern.^25 26^ Effective home programmes must foster self-efficacy, ensuring exercises are relevant, enjoyable and aligned with patient goals. A Cochrane review found that people are more likely to sustain exercise when it is meaningful and enjoyable,^19^ suggesting that personalised, motivational exercise plans are crucial for long-term success.^19 27 28^

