## Methods and analysis

### Study design

This is a single-centre, open-label, randomised controlled feasibility trial of a 12-week SPIN-VR programme with a 24-week post-randomisation follow-up. 50 people diagnosed with knee OA who fulfil National Institute for Health and Care Excellence (NICE) and American College of Radiology (ACR) criteria for a knee OA diagnosis^6 35^ will be randomly assigned in equal numbers to either an SPIN-VR programme or to receive usual care physiotherapy.

The study is planned to run from August 2024 to the end of June 2026 when the last patient follow-up is expected.

The study aims to assess the following feasibility outcomes.

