#### Inclusion criteria

Adults aged 45 years or older.Clinical diagnosis of knee OA.Referred for physiotherapy for clinically diagnosed knee OA pain.Activity-related joint pain.Self-reported knee pain on most days for the past 3 months.Average pain severity in the past week of 4 or greater on a 10-point Numeric Rating Scale.Able to understand written and spoken English.Able to provide written informed consent.

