### Sample size

This feasibility study aims to recruit and randomise 50 participants, a sample size chosen to provide adequate precision in estimating key feasibility parameters, specifically retention and adherence rates, with a 95% confidence intervals of approximately ±10%.^49 50^ As the primary objective is to evaluate feasibility rather than effectiveness, no formal power calculation was performed.^51^ The sample size was pragmatically determined based on an anticipated recruitment rate of approximately four participants per month over a 13-month period, with an estimated 60% of eligible patients expected to consent to participation. This conservative sample size is intended to generate essential data to inform the design and sample size calculations of a future pilot or definitive RCT.

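### The secondary-outcome analysis is worded as change from baseline tested at 0.05 with no between-arm contrast named, so it should state a baseline-adjusted difference between the randomised groups

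*Protocol article*

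**What the plan says.** The Data analysis section is the only place in the protocol article that describes how the clinical outcomes will be analysed. It makes three statements.

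- Purpose: secondary outcomes, including the patient-reported measures, "will be assessed before and after the intervention to establish any possible trend in the intervention effects over time".
- Method: "changes in outcome assessments relative to baseline assessments will be analysed using appropriate parametric or non-parametric statistics", the choice depending on the characteristics of the data.
- Decision rule: "All tests will be two-sided with an alpha level of 0.05".

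The 95% CIs promised in that section belong to eligibility, recruitment, acceptability and adherence. No between-arm difference, and no adjustment for baseline, is mentioned for any clinical outcome.

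The trial is nevertheless a randomised comparison. Under Study design, patients are "randomly assigned in equal numbers to either an SPIN-VR programme or to receive usual care physiotherapy". The Comparator section describes usual care as physiotherapy advice and exercise, and the Safety section says the physical content of SPIN-VR is no different from what usual care would ask of a patient. Entry requires "Average pain severity in the past week of 4 or greater on a 10-point Numeric Rating Scale", and the Introduction notes that "OA pain fluctuates, often with intermittent and severe flares". The Sample size section states that "no formal power calculation was performed".

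**The concern.** A change from baseline within one arm does not identify an intervention effect. It mixes any effect of the VR system with the effect of exercise as such, the natural course of symptoms, and regression to the mean in people enrolled because their recent pain was above a threshold. Randomisation to a concurrent physiotherapy arm is what separates these, and only a contrast between the arms uses it.

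The article links a before-after assessment to intervention effects and attaches a significance level, without naming that contrast. An analyst following the text literally could run paired tests in the SPIN-VR arm and report p-values below 0.05 as a signal for SPIN-VR. What is at stake is the interpretation of the clinical results and the usefulness of the estimates passed to a later trial.

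This is more than detail left to an analysis plan. The article itself fixes a comparison (before against after), an interpretation and an alpha level, and an analysis plan would be expected to follow them.

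**Working it through.** **Inputs from the protocol article.** Total 50, allocated equally, so 25 per arm (Study design, Sample size). Two-sided alpha 0.05 (Data analysis). Entry threshold 4 on the pain scale (Inclusion criteria). Follow-up at 12 and 24 weeks. The article gives no SD, correlation or expected effect for any clinical outcome, so those below are assumptions, shown as ranges.

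**The plan's own figure.** About four patients a month for 13 months gives 4 × 13 = 52, which agrees with the stated 50 to within two patients. The calculations below use 25 per arm with no dropout.

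**Reading A: changes are tested within each arm.**

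Assume screened patients have normally distributed pain scores with mean m of 4 to 6, SD s of 2 or 2.5, and correlation ρ of 0.5 or 0.7 between the qualifying score and follow-up. Only scores of 4 or more are enrolled. There is no treatment effect of any kind.

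- Expected fall from regression to the mean = (1 − ρ) × s × λ, where λ = φ(a) / [1 − Φ(a)] and a = (4 − m)/s.
- Example, m = 4, s = 2, ρ = 0.5: a = 0, λ = 0.798, fall = 0.5 × 2 × 0.798 = 0.80 points.
- Example, m = 6, s = 2, ρ = 0.7: a = −1, λ = 0.288, fall = 0.3 × 2 × 0.288 = 0.17 points.

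Simulating 20,000 trials per scenario, with a paired test in one arm of 25 and a two-sample test of the same changes between arms, gave:

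| m | s | ρ | Within-arm test significant | Between-arm test significant |
|---|---|---|---|---|
| 4 | 2.5 | 0.5 | 55% | 5.0% |
| 4 | 2 | 0.7 | 34% | 5.0% |
| 5 | 2.5 | 0.5 | 30% | 5.0% |
| 5 | 2 | 0.7 | 16% | 5.1% |
| 6 | 2.5 | 0.5 | 15% | 5.1% |
| 6 | 2 | 0.7 | 9% | 5.1% |

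Over all twelve combinations the within-arm figure runs from 8.6% to 55.3% and the between-arm figure from 4.6% to 5.2%. A noncentral-t calculation from the closed form agrees with the within-arm column (for example 0.551 for the first row and 0.085 for the last).

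A general benefit of physiotherapy works the same way. If both arms truly improve by d outcome SDs and SPIN-VR adds nothing, the paired test in 25 patients has noncentrality 5d / √[2(1 − ρ)]. For d = 0.3 and ρ = 0.5 this is 5 × 0.3 / 1 = 1.5, giving 30% significant; at ρ = 0.7 it is 46%. For d = 0.2 the figures are 16% and 24%. The improvement here is real, so these are not false positives for change. The error would be to attribute the change to SPIN-VR.

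**Reading B: change scores are compared between arms.**

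Both influences cancel in expectation, so the estimate is unbiased. Only precision differs. In units of the outcome variance, a change score has variance 2(1 − ρ) and a baseline-adjusted score 1 − ρ². The 95% CI half-width with 25 per arm is 1.96 × √(variance × 2/25).

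| Baseline correlation | Change-score variance | Adjusted variance | Half-width, change score | Half-width, adjusted |
|---|---|---|---|---|
| 0.3 | 1.40 | 0.91 | 0.66 SD | 0.53 SD |
| 0.5 | 1.00 | 0.75 | 0.55 SD | 0.48 SD |
| 0.7 | 0.60 | 0.51 | 0.43 SD | 0.40 SD |

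**The case against.** The strongest reply is that the text does not exclude a between-arm comparison. The abstract describes SPIN-VR as being evaluated against usual care, and comparing change scores between arms is an ordinary reading in a randomised trial. This stands. A reader might infer that the plan discards the randomisation; the wording does not establish that. It establishes that the contrast is left unstated beside language that points to before-after inference.

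It can also be said that the choice between ANCOVA and change scores is usually settled in an analysis plan. That is fair on the model itself. It does not cover the article's link between before-after change and intervention effects.

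The regression-to-the-mean range has limits. It treats the baseline value as the score that qualified the patient, although screening in clinic precedes the baseline visit. It also applies to the past-week pain rating, which is not itself a listed outcome. For measures only loosely tied to that rating, such as the step, sit-to-stand and walk tests, the effect would be smaller.

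Three stronger inferences are tempting and should not be drawn:

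- *Spurious signals are near certain.* If there were 32 tests (some 16 outcomes at two visits), all independent, the chance of at least one p<0.05 would be 1 − 0.95^32 = 81%. Subscales and repeat visits in the same patients are correlated. At common correlations of 0.3, 0.5 and 0.7 a simulation gives 68%, 52% and 35%.
- *Such signals would decide whether a definitive trial goes ahead.* Nothing in the article makes a secondary p-value a criterion for progression. The primary outcomes are feasibility measures, the Introduction leaves efficacy to a larger trial, and the lack of an efficacy power calculation is declared as a limitation.
- *Rank tests would leave the next trial without an SD.* The Data analysis section separately plans variance estimates for future power calculations.

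**Conclusion.** The point holds as a fault of wording with a practical consequence, confined to the secondary outcomes. The contrast needs to be stated on either reading. Read as within-arm tests, the analysis could credit SPIN-VR with improvement it did not cause, at a rate of roughly 9% to 55% from regression to the mean alone, against about 5% between arms. Read as between-arm change scores, it is valid but gives up precision: baseline adjustment lowers the variance by 25% at a correlation of 0.5 (35% at 0.3, 15% at 0.7). The first range depends on the assumed screening mean, SD and correlation, and on the outcome behaving like the entry pain score. The second depends only on the assumed correlation. The change is worth making because it costs almost nothing. It does not bear on the primary feasibility objective.

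**What to change.** Replace the sentence on changes relative to baseline with wording such as: *For each secondary outcome, the mean difference between randomised groups at 12 and 24 weeks, adjusted for the baseline value of that outcome, will be reported with a 95% CI. Within-arm changes will be presented descriptively only. Any p-values are exploratory and will not be used to claim efficacy.* Reword the purpose sentence so that before-after change is not described as showing intervention effects. Reporting the residual SD and the baseline correlation alongside each estimate would also serve the planned sample size work.

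Deleting the alpha statement is optional once p-values are labelled exploratory.

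The cost is a few lines of text. Baseline values of these assessments are already collected, and no extra visits, patients or measurements are needed.

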### Secondary outcome measures

Evaluate the processes for exercise mechanism of action at improving pain outcomes through a variety of measurements relating to muscle strength and endurance, aerobic capacity, exercise technique, central pain processing, and self-reported pain outcomes and moderators.Assess intervention to treat knee OA using the Outcome Measures in Rheumatology—Osteoarthritis Research Society International (OMERACT-OARSI) core domain set. A variety of patient-reported outcome measures. Pain sensitisation by algometer. Dynamic balance using a step test.

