### Trial assessments

An assessment will be carried out at the baseline and consent visit with a researcher. During the baseline visit, the research team will collect demographic data. Patients will have two in-person follow-up assessments with the Cardiff University (CU) research team, at 12 weeks post randomisation, which will occur at the end of their SPIN-VR programme, and another at 24 weeks post randomisation. A flowchart of the patient pathway is presented in figure 1.

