**Figure 1 F1:**
[figure not shown]
Flow diagram of patient study pathway of recruitment and follow-up. CSRI, Client Service Receipt Inventory; IPAQ, International Physical Activity Questionnaire; PHQ9, Patient Health Questionnaire-9; SPIN-VR, Sensor-based Physiotherapy Intervention with Virtual Reality.

The following assessments will be conducted at both baseline and follow-up visits:

Pain sensitisation, conducted using algometer.Dynamic balance, using a validated step test by asking participants to maintain balance on the study leg, while stepping the contralateral leg on and off a 15 cm step as many times as possible in 15 s without any weight transfer to the stepping leg. A higher number of steps indicates a better outcome.Evaluation of exercise mechanisms of action:Muscle strength and endurance: 30 s time sit to stand test. A faster time indicates a better outcome.^38^Aerobic capacity: timed 6 m walk test. A faster time indicates a better outcome.^39^Exercise technique: throughout exercises by evaluating key biomechanical parameters for each exercise and compared with lab-based data collected on healthy subjects, for example, centre of mass motion.Central pain processing: quantitative sensory testing modality of pressure pain detection thresholds local and distant from the index knee.^40^Self-report measures of pain mechanisms and moderators: activity, medication use, psychological well-being.^41^

Participants will be invited to complete a series of patient-reported outcomes measures (PROMs). These are:

Knee Osteoarthritis Outcome Score (pain, symptoms, activities of daily living, function in sport and recreation, and knee-related quality of life). A higher score indicates a better outcome.^42^EQ-5D-5L Questionnaire (overall health status).^43^Client Service Receipt Inventory (healthcare utilisation, medication use, service receipt for arthritis).^44^International Physical Activity Questionnaire^45^ (physical activity levels).Self-Efficacy for Managing Chronic Diseases 6-Item Scale (confidence in managing chronic disease) A higher score indicates a better outcome.^46^Central Aspects of Pain (constructs associated with pain across musculoskeletal conditions).^47^Pain intensity before and after exercise. A lower score indicates a better outcome.A patient acceptability questionnaire on the SPIN-VR intervention.

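### A blanket two-sided 0.05 threshold for about 16 secondary measures in a trial not powered for efficacy: report exploratory estimates with 95% CIs instead

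*Protocol article*

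**What the plan says.** In the protocol article, Data analysis says that "changes in outcome assessments relative to baseline assessments will be analysed using appropriate parametric or non-parametric statistics based on the characteristics of the data", and then that "All tests will be two-sided with an alpha level of 0.05". It does not say whether change is tested within each arm or compared between arms. It gives the purpose of the secondary analysis as "to establish any possible trend in the intervention effects over time and understand the variability in data".

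Secondary outcome measures includes the aim "Assess intervention to treat knee OA using the Outcome Measures in Rheumatology" and the rest of that core domain set. The assessments listed with Figure 1 include "Knee Osteoarthritis Outcome Score (pain, symptoms, activities of daily living, function in sport and recreation, and knee-related quality of life", which is five scores from one instrument, plus further questionnaires, pressure pain thresholds and performance tests. Trial assessments places the follow-up visits "at 12 weeks post randomisation, which will occur at the end of their SPIN-VR programme, and another at 24 weeks post randomisation". Neither visit is named as leading, nor is any clinical outcome.

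Sample size states: "As the primary objective is to evaluate feasibility rather than effectiveness, no formal power calculation was performed". The strengths and limitations box also concedes that there is no power calculation for efficacy.

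**The concern.** A fixed significance threshold is a decision rule. It sorts results into significant and not significant, and here it applies to every secondary measure of a 50-patient feasibility trial. The stated aims for these data are to look for trends, to understand variability and to inform the sample size of a later trial. Estimates and intervals serve those aims; a 0.05 cut-off does not.

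The risk is misreading in both directions. With many tests and no stated adjustment, one or more nominally significant results can easily arise by chance and be taken as a signal. With few patients, a non-significant result can be taken as absence of effect. Either could colour the choice of primary outcome for the future trial that these data are meant to inform.

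**Working it through.** **The plan's own figures.** The article states no family-wise error rate, so there is none to reproduce. The sample size is consistent with its recruitment basis: 4 per month × 13 months = 52, against 50 planned. Equal allocation (Study design) gives 25 per arm.

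**Number of measures** (list with Figure 1):
- knee outcome score domains: 5
- EQ-5D-5L, physical activity, self-efficacy, Central Aspects of Pain, pain around exercise: 5
- pressure pain thresholds, local and distant: 2
- step test, sit to stand, walk test: 3
- exercise technique: 1

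Total: 16. Counting the service receipt inventory instead of exercise technique also gives 16; counting both gives 17. Two follow-up visits give 16 × 2 = 32 tests if every measure is tested at both. The article does not say that, so 16 and 32 are both carried forward.

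**Between-arm tests, no effect, independent outcomes.** The chance of at least one result below 0.05 is 1 − 0.95^k.
- k = 16: 1 − 0.95^16 = 56.0%
- k = 32: 1 − 0.95^32 = 80.6%; expected number 32 × 0.05 = 1.6
- favouring SPIN-VR only: 1 − 0.975^16 = 33.3% and 1 − 0.975^32 = 55.5%

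**Between-arm tests, no effect, correlated outcomes.** The article gives no correlations, so these are assumed. Two-sample t tests were simulated with 25 per arm, 16 outcomes and 2 visits (4,000 runs per row):

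| Correlation between outcomes | Correlation between visits | Any of 32 | Favouring SPIN-VR, of 32 | Any of 16 (one visit) |
|---|---|---|---|---|
| 0.3 | 0.5 | 70.1% | 38.0% | 47.9% |
| 0.3 | 0.7 | 67.2% | 36.5% | 47.4% |
| 0.5 | 0.5 | 58.5% | 30.8% | 37.6% |
| 0.5 | 0.7 | 55.0% | 29.4% | 37.7% |
| 0.7 | 0.5 | 43.8% | 22.2% | 27.0% |
| 0.7 | 0.7 | 40.5% | 21.1% | 26.8% |

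A second simulation used equally correlated normal statistics. At correlations of 0.3, 0.5 and 0.7 it gave 68.1%, 52.1% and 34.8% for 32 tests, and 47.6%, 37.5% and 26.4% for 16. Together the ranges are about 35% to 70% (32 tests) and 26% to 48% (16 tests) for any result, and 21% to 38% for one favouring SPIN-VR among 32.

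**Within-arm tests.** The figures above do not describe these, because their null is no change over time. Entry requires average pain of at least 4 (Inclusion criteria), so regression to the mean is expected. The Introduction describes osteoarthritis pain as fluctuating, and both arms receive exercise-based physiotherapy. Significant change within the SPIN-VR arm could therefore arise without any effect specific to SPIN-VR, and a stricter alpha would not remove that bias.

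**Non-significant results.** For an assumed standardised difference d = 0.5 with 25 per arm (normal approximation), power = Φ(0.5 × √(25/2) − 1.96) = Φ(1.768 − 1.960) = Φ(−0.192) ≈ 42%. A true difference of that size would be missed more often than found.

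**Would adjustment help?** Bonferroni levels are 0.05/16 = 0.0031 and 0.05/32 = 0.0016. Power for d = 0.5 then falls to about 12% and 8%. Adjustment is therefore a poor remedy here, and it leaves the within-arm problem untouched.

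**The case against.** The strongest reply is that nothing confirmatory is planned. The title, objective and primary outcomes concern feasibility, the clinical measures are labelled secondary, and the lack of efficacy power is admitted. The analysis aims speak only of a possible trend and of variability. Family-wise error matters most when one rejection would support a claim, and no such claim is announced. A hierarchy or adjustment may also sit in the full protocol or SAP, which are not shown. This largely stands: the missing hierarchy and adjustment are not the finding. What remains is the sentence that the article does fix, a 0.05 rule for all tests.

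A reader might infer that a spurious significant benefit of SPIN-VR is likely. The documents do not support that. No between-arm test is specified, the number of tests is inferred, and chance results can favour either arm. In the SPIN-VR direction the chance exceeds 50% only when all 32 tests are made and are nearly independent.

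A reader might also see a contradiction with the Sample size section. There is none: an alpha level can be stated without a power calculation. The two sit badly together because the threshold has little use in a trial of this size. Nor does the article link any secondary p-value to the go-ahead for a larger trial, so harm by that route is possible but not planned.

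**Conclusion.** The concern holds in limited form. The article fixes an unadjusted two-sided 0.05 threshold for all tests on about 16 secondary measures in a trial not powered for efficacy, and results on either side of that threshold would be hard to interpret. For between-arm tests under no effect, the chance of at least one nominal finding is several times the nominal 5% in every scenario examined; in the SPIN-VR direction among 32 tests, 21% to 38% compares with a nominal 2.5% for a single test. These sizes rest on the inferred count of 16 or 32 tests and on assumed correlations of 0.3 to 0.7. For within-arm tests the objection is bias, and no rate is claimed. Severity is minor to moderate: the feasibility conclusions are unaffected, and secondary status already supplies part of the context that an exploratory label would give.

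**What to change.** Replace the alpha sentence in Data analysis with, for example: *Secondary clinical and mechanistic outcomes are exploratory. They will be reported as between-arm estimates with 95% confidence intervals and measures of variability, without significance tests, and no claim of efficacy will be based on them.* Optionally, name in advance one outcome at one visit as the candidate primary for the future trial, such as the knee outcome score pain domain at 12 weeks. The planned variance estimates for future power calculations can stay.

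This also settles which contrast is reported. The cost is one or two sentences in the analysis section or SAP, with no extra patients or data. The downside is that p-values for these outcomes are no longer presented.

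### The plan names only an unspecified outcome variance for sizing the future trial; since baselines are collected, the baseline-adjusted residual variance and the baseline to follow-up correlation should be estimated as well

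*Protocol article*

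**What the plan says.** The Data analysis section of the protocol article names one quantity, and a rule for its uncertainty: "Estimates of population variances of outcomes for future power calculations will use the upper 80th percentile of confidence intervals". The Sample size section makes such inputs part of the study's purpose, describing the sample as "intended to generate essential data to inform the design and sample size calculations of a future pilot or definitive RCT".

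Paired measurements exist for the clinical outcomes. For the performance and mechanistic tests, Trial assessments says "The following assessments will be conducted at both baseline and follow-up visits". For the secondary outcomes generally, Data analysis says "Secondary outcome measures, including PROMs, will be assessed before and after the intervention".

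The same section also plans that "changes in outcome assessments relative to baseline assessments will be analysed using appropriate parametric or non-parametric statistics". Thus the outcome whose variance is meant could be the follow-up value or the change. The article does not say which. It fixes no primary outcome, effect size, power or analysis model for the future trial, and gives no correlation.

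**The concern.** When a continuous outcome is measured at baseline and follow-up on the same scale, a definitive trial can be analysed by regressing follow-up on baseline and arm. Its sample size then depends on the variance left after that adjustment. A variance of follow-up values, or of changes, is not that quantity, and the adjusted variance cannot be recovered from either one alone without the correlation.

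This feasibility study collects the paired data that supply the missing piece. If it reports only the variance that the article names, a later planner has two problems: not knowing which variance was reported, and having no basis in the report for taking credit for baseline adjustment. The likely result is a planned trial larger than necessary. The planned upper confidence limit then adds its caution to the larger base.

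The point is which variance is estimated. It does not concern how the 80% limit is defined or how this study tests its own outcomes.

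**Working it through.** **Inputs from the article.** 50 randomised ("This feasibility study aims to recruit and randomise 50 participants"), in equal numbers ("will be randomly assigned in equal numbers to either an SPIN-VR programme or to receive usual care physiotherapy"). For this study's tests, "All tests will be two-sided with an alpha level of 0.05"; I assume the same for the future trial.

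**Assumptions, because the article gives no figures.** Rho from 0.3 to 0.7; equal variance sigma^2 at baseline and follow-up and in both arms; a baseline-adjusted future analysis; for the example, 90% power and a difference of 0.4 SD.

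**The plan's own figure.** No sample size is stated for the future trial, so there is none to reproduce. The feasibility sample size is consistent with its recruitment basis: 4 per month × 13 months = 52, against 50.

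**Step 1: the three candidate variances.**
- Follow-up value: sigma^2
- Change from baseline: 2·sigma^2·(1 − rho)
- Residual after regression on baseline: sigma^2·(1 − rho^2)

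Sample size is proportional to the variance used. The excess over baseline-adjusted sizing is therefore:
- follow-up variance: 1/(1 − rho^2) − 1
- change variance: 2(1 − rho)/(1 − rho^2) − 1 = 2/(1 + rho) − 1

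**Step 2: results.**

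| Assumed rho | Excess, follow-up variance | Excess, change variance |
|---|---|---|
| 0.3 | 10% | 54% |
| 0.4 | 19% | 43% |
| 0.5 | 33% | 33% |
| 0.6 | 56% | 25% |
| 0.7 | 96% | 18% |

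Both are positive for every rho between 0 and 1, but they move in opposite directions as rho rises. The two readings agree only at rho = 0.5.

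**Step 3: example per arm.** On the follow-up variance, 2·(1.96 + 1.2816)^2/0.4^2 = 131.3.
- At rho = 0.5: residual variance gives 131.3 × 0.75 = 98.5. The change-variance multiplier is 2(1 − 0.5) = 1, so that basis stays at 131.3.
- At rho = 0.6: residual variance gives 131.3 × 0.64, about 84. The change-variance multiplier is 2(1 − 0.6) = 0.8, giving 131.3 × 0.8, about 105.

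**Step 4: the upper 80% limit.** On a one-sided reading, the factor on a pooled within-arm variance is df/chi2(0.20, df). It is 1.21 at df = 50 − 2 = 48, and 1.24 at df = 38 (40 completers, assumed). The residual variance has one degree of freedom fewer, so its factor is nearly the same and practically cancels from the ratios in step 2. It is not part of the excess.

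**Step 5: how well this study can estimate rho.** With 40 completers and an observed rho of 0.5, the Fisher 95% CI is 0.22 to 0.70, an excess on the follow-up reading of about 5% to 97%. With 50 completers the interval is 0.26 to 0.68. A one-sided 80% lower limit with 50 completers turns an observed 0.5 into 0.40, which cuts the excess from 33% to 19%.

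**The case against.** The strongest reply is that the article states nothing false. An outcome variance is itself an ingredient of the adjusted variance, so planning to estimate it is not an error. The article is a condensed document and nowhere says that the correlation will not be estimated; the full protocol or analysis plan may list it. The Dissemination policy promises a public anonymised participant-level dataset and code, so the correlation can be computed later. It would also be imprecise here, and leaving it out errs towards adequate power.

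Most of this stands, and it limits the point. A reader might infer that the plan carries forward a raw follow-up variance and nothing else, so that the definitive trial would be a third or more too large. The documents do not support that. The text does not say which variance is meant. A third or more needs rho of at least 0.5 on the follow-up reading, and on the change reading the excess falls below a third once rho passes 0.5. Both readings also need a baseline-adjusted future analysis and planners who ignore a correlation available in the same data. None of this is fixed in the article.

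Two things survive. The article did more than stay silent: it chose a planning quantity and a confidence limit for it, and left that quantity ambiguous. And imprecision in rho argues for planning from an upper limit on the residual variance, which carries that uncertainty, more than for omitting the residual variance.

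**Conclusion.** The concern holds in a conditional form. The only input named for future power calculations is a variance whose definition is unclear, and under either definition it exceeds the variance relevant to a baseline-adjusted trial. Over the assumed rho of 0.3 to 0.7, the overstatement is 10% to 96% for follow-up variance and 54% down to 18% for change variance.

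The direction does not depend on the reading; the size does, and it also depends on a correlation that the documents do not give. The loss is recoverable from the promised public dataset. I rate this a worthwhile, low-cost improvement to a stated deliverable. A reader might go further and conclude that the definitive trial would look unaffordable; with no effect size, power or primary outcome fixed for that trial, the documents give no basis for this.

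**What to change.** In Data analysis:

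1. State whether the variances for future power calculations are of follow-up values or of changes from baseline.
2. For each candidate outcome measured at both times in both arms, also estimate the residual variance from a regression of follow-up on baseline and arm, and apply the planned upper 80% limit to it.
3. Report the baseline to follow-up correlation with its 95% CI beside the within-arm variance.

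The cost is one regression per outcome on data already collected, with no added patients, visits or measurements. The drawback is that with about 40 to 50 completers the correlation is imprecise, so future planning should use the upper limit of the residual variance and not its point estimate.
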